# Efficacy of tranexamic acid versus placebo in reducing blood loss during burn excisional surgery: a multi-center, double-blind, parallel, randomized placebo-controlled clinical trial (TRANEX)

**DOI:** 10.1186/s13063-024-08332-1

**Published:** 2024-08-02

**Keywords:** Tranexamic acid, Burns, Excisional surgery, Blood loss, Fibrinolysis

## Abstract

**Background:**

Despite an increase in knowledge, blood loss during burn excisional surgery remains a major challenge and is an independent predictor of mortality. During burn surgery, limited measures are available to control the bleeding. Increased fibrinolysis could be one of the contributing factors of blood loss during burn excisional surgery. Tranexamic acid inhibits the fibrinolytic response, and a small body of evidence shows positive effects of tranexamic acid on the volume of blood loss.

**Methods:**

The main objectives of this study are twofold, (1) to investigate whether tranexamic acid reduces blood loss and (2) to investigate the changes in coagulation after burn trauma and during burn excisional surgery. This study is a multicenter double-blind randomized clinical trial in patients scheduled for burn excisional surgery within the Dutch burn centers. All adult patients scheduled for burn surgery with an expected blood loss of ≥ 250 are eligible for inclusion in this study. The study is powered on a blood loss reduction of 25% in the intervention group. In total, 95 subjects will be included. The intervention group will receive 1500 mg tranexamic acid versus placebo in the other group. Primary endpoint is reduction of blood loss. Secondary endpoints include occurrence of fibrinolysis during surgery, graft take of the split skin graft, and differences in coagulation and blood clot formation.

**Discussion:**

This protocol of a randomized controlled trial aims to investigate the efficacy of tranexamic acid in reducing blood loss during burn excisional surgery. Furthermore, this study aims to clarify the coagulation status after burn trauma and during the surgical process.

**Trial registration:**

EudraCT: 2020-005405-10; ClinicalTrial.gov: NCT05507983 (retrospectively registered in August 2022, inclusion started in December 2021).

## Administrative information

Note: the numbers in curly brackets in this protocol refer to SPIRIT checklist item numbers. The order of the items has been modified to group similar items (see http://www.equator-network.org/reporting-guidelines/spirit-2013-statement-defining-standard-protocol-items-for-clinical-trials/).

## Introduction

### Background and rationale {6a}

Major burn trauma involves a complex interplay between activation of coagulation and activation of the immune system [1]. Although the underlying pathophysiology behind these processes is not completely understood, more knowledge became available in recent years. Following severe burn injury, the patient’s coagulation status may change considerably as a response to the systemic inflammatory response and as a result of interventions such as hemodilution and during fluid resuscitation and excisional surgery [2]. The development of coagulopathy has been identified as a risk factor for increased morbidity and mortality after major burn trauma [3, 4]. Despite an increase in knowledge, blood loss during burn excisional surgery remains a major challenge and is an independent predictor of mortality [5]. During burn excisional surgery, limited interventions are available to control the bleeding during surgery. For example, the use of topical adrenalin and topical tranexamic acid and the use of a tourniquet have been described in literature [6]. Despite these techniques, blood loss is still substantial [7].

Cell salvage is a well-known method to reduce allogenic blood transfusion during high blood loss surgery. The use of cell salvage is feasible in burn patients and up to 25% of blood loss can be recovered. However, despite strict sterile handling of shed blood, the erythrocyte concentrate showed substantial bacterial contamination [8].

Reducing blood loss and tailoring blood product administration may improve patient outcome and reduce morbidity and mortality associated with transfusion and blood loss [3]. Therefore, well-functioning coagulation is of the upmost importance.

Normally, coagulation is a balanced process in which there is simultaneous coagulation and fibrinolysis. However, several studies describe a disruption of the immune system and coagulation comparable to changes after major trauma [3, 9, 10]. Marked increase of activation in coagulation paradoxically coexisted with an increase of fibrinolysis [4, 9, 11].

The increased fibrinolysis could be one of the contributing factors of blood loss during burn excisional surgery as fibrinolysis is seen in burn patients [9]. Furthermore, moderate to severe disturbance of the fibrinolytic system is seen in > 50% of all trauma patients [12].

Tranexamic acid inhibits the fibrinolytic response by inhibiting the conversion of plasminogen to plasmin. Normally, plasmin breaks down fibrin to fibrin degradation products thereby weakening the clot. By lowering the concentration of plasmin by the administration of tranexamic acid, the breakdown of the cloth will be inhibited. There is some body of evidence suggesting the beneficial effect of tranexamic acid on the perioperative blood loss and transfusion [13–15]. A small blinded randomized prospective study found a reduction of 36% in blood loss in 27 tangential burn excisions by administrating 20 mg/kg tranexamic acid intravenous [13], while a small RCT with 50 patients performed in India showed a reduction of 41% of perioperative blood loss with 15 mg/kg tranexamic acid intravenous [14]. Furthermore, a retrospective study reported a 30% decrease in transfusions during burn excisional surgery by administration of 10 mg/kg tranexamic acid intravenous followed by a continuous infusion of 1 mg/kg/h [15]. However, no study investigated the fibrinolytic state of burn patients during burn excisional surgery. There is sufficient evidence available for the safety of the use of tranexamic acid in other patient categories. Several large studies, CRASH-II and III trial [16, 17], WOMAN-trial [18], and a recent retrospective case–control study [19], have investigated possible thromboembolic complications of the use of tranexamic acid in trauma patients, during orthopedic surgery and women with postpartum hemorrhage, and reported no higher incidence in any complication in the tranexamic acid group.

The perioperative monitoring of coagulation and especially fibrinolysis using classic hemostatic tests is difficult [3]. More real-time test like thrombelastography (TEG) or rotational thromboelastometry (ROTEM) could give insight especially in the state of the fibrinolytic system [1, 10]. Schaden et al. reported a reduction in transfusion during burn excisional surgery by using a coagulation management protocol including ROTEM [9, 20]. While ROTEM is promising, ROTEM could miss moderate fibrinolysis [12]. To further study the fibrinolytic system, more in-depth laboratory tests are needed. For example, plasmin-α2-antiplasmin complex is a separate test and is a more sensitive parameter to investigate the occurrence of fibrinolysis.

The main goal of this study is twofold. First is to investigate the ability of tranexamic acid to reduce blood loss and blood transfusion during burn excisional surgery. Second is to investigate the occurrence and magnitude of fibrinolysis during burn excisional surgery.

### Objectives {7}

#### Research hypothesis

Tranexamic acid reduces the volume of blood loss during burn excisional surgery, irrespectively of the presence of hyper fibrinolysisDuring burn surgery, a significant effect of hyper fibrinolysis is present due to the stress of burn trauma

#### Primary objective

To determine whether tranexamic acid reduces the volume of blood loss compared to placebo in patients undergoing burn excisional surgeryTo determine the occurrence and extent of fibrinolysis during burn excisional surgery

#### Secondary objective

To investigate the influence of tranexamic acid of the graft take/loss

### Trial design {8}

The TRANEX-study is designed as a double-blind, placebo-controlled, randomized superiority trial with two parallel groups and primary endpoint of blood loss during surgery. In total, 95 patients will be allocated to either tranexamic acid or placebo. A variable block randomization will be used stratified by center in which the patient is enrolled. The investigators, participants, and surgeon as well as the statistical procedure will be blinded. Analysis will be performed with the intention to treat principle.

## Methods: participants, interventions, and outcomes

### Study setting {9}

This multicenter study is a collaboration between all dedicated burn centers in the Netherlands: Maasstad Hospital in Rotterdam, Martini Hospital in Groningen, and the Red Cross Hospital in Beverwijk. Participant recruitment will be from patients scheduled for burn excisional surgery with an expected blood loss of > 250 ml. The surgery and study procedures will be performed in the designated center in which the patient is scheduled for surgery.

### Eligibility criteria {10}

#### Inclusion criteria

Patients scheduled for burn excisional surgeryAn expected blood loss of ≥ 250 ml based on the estimation by the performing surgeon based on:◦ ≥ 2% body surface area excision planned (100–200 cc/%BSA excised, based on retrospective data from Burn Centre Rotterdam)◦ Operation technique used (some techniques show more blood loss than others)◦ Time after burn trauma (i.e., expected healing and subsequently the extent of bleeding)  ≥ 18 years oldInformed consent of patient or legal representativePatients or legal representative should have enough knowledge of Dutch to provide informed consent

### Exclusion criteria

Patients with a recorded coagulopathy in their historyThe use of anticoagulants (except acetylsalicylic acid or (intensive) prophylaxis low-molecular weight heparin > 12 h before surgery)Severe kidney failure (creatinine > 500 μmol/L)Allergy for tranexamic acidDiagnosis of acute venous/arterial thrombosis within 3 months before inclusionDiffuse intravascular coagulation (based on the DIS-score > 5)PregnancyActive breastfeedingHistory of epilepsy

### Who will take informed consent? {26a}

The main physician will ask the patient’s consent for a member of our study team to approach the patients with information regarding this study. The study team consist of research nurses and junior and senior investigators; the whole team is trained by the Good Clinical Practice guidelines (ICH E6 GCP): GCP-WMO or (e)BROK©.

The member will orally explain the study, provide additional written information, and answer possible questions; hereafter, there is a reflection time of a minimum of 24 h. After at least 24 h, the study member returns to the possible participant, and there is a possibility to discuss the study and possible questions. If the participants agree to participate in this study, written consent will be obtained. Informed consent will be gained from the participants, provided that she/he is able to understand the patient information and consider the pros and cons of study participation. If the participants can provide informed consent for the operation and anesthesia, the patient is able to consider participation and give informed consent for this study. In participants who are cognitively impaired or sedated in the ICU department, a legal representative will be asked to consider study participation and give informed consent. The participants will be asked for written informed consent when they regain the ability to provide informed consent.

### Additional consent provisions for collection and use of participant data and biological specimens {26b}

This is not applicable for the samples taken for the main purpose is to answer the research question. Participants are specifically asked for permission to store the samples for 5 years for future research.

## Interventions

### Explanation for the choice of comparators {6b}

At the moment, there is limited body of evidence suggesting the beneficial effect of tranexamic acid on the perioperative blood loss and transfusion [13–15]. However, there is insufficient evidence as there are no large randomized controlled trials available to make a definite conclusion. Therefore, tranexamic acid will be compared to placebo to evaluate the efficacy of tranexamic acid.

### Intervention description {11a}

Patients will be prepared for surgery and anesthetized following the current standard of care. Both the placebo as the tranexamic acid will consist of an infusion bag of a total volume of 100 ml and will be indistinguishable for study personnel. See Fig. 1 for the complete timeline of study procedures. During induction of anesthesia, but before incision, the study medication will be administered over a period of 15 min, not surpassing the maximum delivery rate of tranexamic acid of 100 mg/minute. The intervention group will receive 1500 mg tranexamic acid intravenous. The placebo group will receive a sodium chloride 0.9% bolus.

**Fig. 1 Fig1:**
[figure not shown]
SPIRIT figure, schedule of enrolment, interventions, and assessments. -t_1_: > 24 h before surgery; t_1_: pre-surgery; t_2_: after anesthesia induction but before incision; t_3_: 1 h after incision; t_4_: during closure if total surgery time > 1.5 h; t_5_: end of surgery; t_6_: > 6 h after finishing surgery. *Blood samples*: hemoglobin, electrolytes (sodium/potassium), kidney function (urea/creatinine), albumin. *Basic coagulation*: INR, APTT, thrombocytes and fibrinogen. *Additional coagulation*: plasminogen activator inhibitor, D-dimer, global fibrinolysis, thrombin generation fVII, von-Willebrand Factor and anti-thrombin III and stored serum. *Complications*: cardiopulmonary or neurologic complication within the 3 months after the study period. ROTEM, rotational thromboelastometry

Blood loss is difficult to measure; therefore, we will have a dedicated person available to monitor and register blood loss and measure the size of the excision. To determine the size of the excision, the excision site will be measured using a ruler. To register blood loss, we will use two methods. Firstly, intraoperative blood loss will be estimated by measuring the volume of blood collected in suction canisters, the weight of blood-soaked material (gauzes, pads, etc.), and the volume of adrenalized saline and subtracting the dry weight of these materials and the volume of adrenalized saline used for cleaning the surgical site. Secondly, we will calculate blood loss based on the preoperative hematocrit, postoperative hematocrit, and the intraoperative transfusions using the formula proposed by Camarase et al. in 2006 [21]. We will use this method because intraoperative transfusions are incorporated in the formula [21].

$$\begin{array}{c}\mathrm{Total}\;\mathrm{blood}\;\mathrm{loss}\;(\mathrm{ml})\;=\;\mathrm{total}\;\mathrm{red}\;\mathrm{cell}\;\mathrm{loss}\;(\mathrm{ml})\;/\;(\mathrm{hematocrit}\;\mathrm{before}\;\mathrm{surgery}\;-\;\mathrm{hematocrit}\;\mathrm{after}\;\mathrm{surgery})\\\mathrm{Total}\;\mathrm{red}\;\mathrm{cell}\;\mathrm{loss}\;(\mathrm{ml})\;=\;\mathrm{accepted}\;\mathrm{red}\;\mathrm{cell}\;\mathrm{loss}\;(\mathrm{ml})\;+\;\mathrm{volume}\;\mathrm{of}\;\mathrm{transfused}\;\mathrm{red}\;\mathrm{blood}\;\mathrm{cells}\\\mathrm{Accepted}\;\mathrm{red}\;\mathrm{cell}\;\mathrm{loss}\;=\;\mathrm{Estimated}\;\mathrm{volume}\;\ast\;(\mathrm{hematocrit}\;\mathrm{before}\;\mathrm{surgery}\;-\;\mathrm{hematocrit}\;\mathrm{after}\;\mathrm{surgery})\\\mathrm{Estimated}\;\mathrm{volume}\;\mathrm{in}\;\mathrm{men}\;=\;\mathrm{weight}\;(\mathrm{kg})\;\ast\;70\;\mathrm{in}\;\mathrm{women}\;\mathrm{weight}\;(\mathrm{kg})\;\ast\;65\;(\mathrm{formula}\;\mathrm{of}\;\mathrm{Moore})\end{array}$$

Blood sample will be taken at three time points during the intervention: before surgery, 1 h after incision, and 6 h after finishing surgery. The blood samples consist of the following analysis: before surgery: hemoglobin, electrolytes (sodium/potassium), kidney function (urea/creatinine), albumin, ROTEM, basic coagulation test (INR/APTT/thrombocytes/fibrinogen); during surgery: ROTEM; after surgery: hemoglobin and hematocrit. In addition to the above-described analysis, additional blood samples will be taken in all patients studied in the Maasstad Hospital. When surgery is ≥ 1.5 h, an additional ROTEM will be determined at the end of surgery. Furthermore, in the Maasstad Hospital, additional samples will be collected to investigate the burn coagulopathy during the perioperative period (i.e., global fibrinolysis, D-dimer, anti-thrombin III, etc.).

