### Relevant concomitant care permitted or prohibited during the trial {11d}

Correction of coagulation and transfusion will be at the discretion of the attending anesthesiologist. The laboratory results taken for this study will not be available for the attending anesthesiologist. Furthermore, the perioperative surgical hemostatic measures (i.e., adrenaline-soaked gauzes and subcutaneous adrenaline injection) will be at de discretion of the performing surgeon appropriate to the local protocol. As such, the concomitant care remains similar between groups.

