### Outcomes {12}

Primary outcome:The volume of blood loss in milliliter/% BSA excised measured during surgery

Secondary outcome:The occurrence and magnitude of fibrinolysis/coagulopathy during burn excisional measured by, among others, ROTEM-analysis, the measurement of global fibrinolysis and D-dimerGraft take of the split skin graft on the area of excision measured in the percentage of vital graft 5 days surgeryHospital mortalityLength of (ICU) stayCardiopulmonary (i.e., arterial embolism)/ neurologic complication (i.e., stroke) (at 3 months after the study procedure)Need for escape medication (tranexamic acid 1000 mg) in case of uncontrolled bleedingThe need for red blood cell transfusion peri-procedural

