### Participant timeline {13}

When a potential participant is scheduled for burn excisional surgery, the patient is informed about the study and informed consent is taken. See Fig. 1 for the complete timeline for the participant. Informed consent is usually taken in the 2-3 days before surgery. After consent, the patients are randomized. A blood sample is taken before surgery to establish a baseline. During surgery, two more blood sample will be taken, and one blood sample will be taken 6–12 h after surgery. Hereafter, the study procedure is finished for the patient. After 3 months, the patient will be contacted to inform whether cardiopulmonary of neurologic complications have occurred.

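### The hematocrit-based blood loss adds back only intraoperative transfusions but uses a hematocrit drawn 6 h or later after surgery, so red cells given in between lower the calculated loss

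*Protocol article*

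**What the plan says.** Intervention description {11a} sets out two measures of blood loss. The first adds suction volume and the weight of soaked material, then subtracts dry weight and rinsing fluid. For the second, "we will calculate blood loss based on the preoperative hematocrit, postoperative hematocrit, and the intraoperative transfusions". The reason given for the choice repeats the same window: "We will use this method because intraoperative transfusions are incorporated in the formula". The formula printed below it adds a transfused-red-cell volume and gives no time limit for it.

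The same section lists the tests by sample: "during surgery: ROTEM; after surgery: hemoglobin and hematocrit". In the text shown, the postoperative hematocrit therefore belongs to the after-surgery sample. Its timing appears in three forms:

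- Intervention description {11a}: "before surgery, 1 h after incision, and 6 h after finishing surgery"
- Fig. 1 legend, t6: "> 6 h after finishing surgery"
- Participant timeline {13}: "one blood sample will be taken 6–12 h after surgery"

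On transfusion, Relevant concomitant care {11d} says: "Correction of coagulation and transfusion will be at the discretion of the attending anesthesiologist". Outcomes {12} defines the primary outcome as "The volume of blood loss in milliliter/% BSA excised measured during surgery" and does not say which of the two methods supplies it.

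**The concern.** A hematocrit method is a red-cell balance: what was lost equals the fall in circulating red cells plus what was put back. Both terms must cover the same interval. Here the fall is taken from before surgery to at least 6 h after it, while the amount put back stops at the end of surgery. A unit given in recovery or intensive care before the draw restores the hematocrit without entering the formula, so the loss it replaced disappears from the result.

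Plans for assessment and collection of outcomes {18a} presents the twofold measurement as a way to gain accuracy. If the second measure is wrong in some patients, it cannot serve as a check on the first.

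**Working it through.** **The plan's own figure.** A 25% reduction from 194 is 48.5 ml/% BSA. With SD 81, two-sided 5% and 80% power, the normal approximation gives 44 per arm and the t-test 44.8, so 45. Then 90 / 0.95 = 94.7, so 95. The stated sample size reproduces, and this point does not affect it.

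**Inputs.** From the protocol's formula: blood volume V = 70 ml/kg in men. Assumed, because the documents do not give them: weight 80 kg, starting hematocrit H0 = 0.38, true red-cell loss L = 300 or 700 ml, one unit = 180 ml red cells (range 150 to 200), and division by the mean of the two hematocrits.

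**Step 1, the balance.** V = 80 × 70 = 5600 ml. Let T be all red cells given before the draw and C the part that is counted.

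- Hematocrit at the draw: H1 = H0 − (L − T)/V
- Calculated red-cell loss: R = V(H0 − H1) + C = L − T + C

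If everything is counted, C = T and R = L. If only intraoperative units are counted, R = L − (red cells given after surgery). The error is one for one, whatever the weight or hematocrit.

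**Step 2, in volumes of blood.** Loss = R / mean hematocrit, with no intraoperative transfusion.

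| True red-cell loss | No unit given | One postoperative unit, not counted | Same unit, counted |
|---|---|---|---|
| 300 ml | H1 0.326; 300/0.3532 = 849 ml | H1 0.359; 120/0.3693 = 325 ml | 300/0.3693 = 812 ml |
| 700 ml | H1 0.255; 700/0.3175 = 2205 ml | H1 0.287; 520/0.3336 = 1559 ml | 700/0.3336 = 2099 ml |

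Against the same patient without the unit, the shortfall is 1 − 325/849 = 62% and 1 − 1559/2205 = 29%. Against the same patient with the unit counted, it is 180/300 = 60% and 180/700 = 26%. The small difference arises because the unit also raises the mean hematocrit.

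**Step 3, range.** On the counted-versus-uncounted comparison, a unit of 150 to 200 ml gives 50 to 67% at 300 ml and 21 to 29% at 700 ml. Two uncounted units at 700 ml give 43 to 57%.

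**Step 4, what pushes the other way.** Split the loss into an intraoperative part and a part lost between the end of surgery and the draw. Then R = intraoperative loss + postoperative loss − uncounted postoperative transfusion. Fluid dilution at the draw lowers H1 and raises R further. As an estimate of intraoperative loss, R can therefore err in either direction.

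**Step 5, the printed last line.** The article divides by the hematocrit difference, not a mean. Without counted transfusion this gives V(H0 − H1)/(H0 − H1) = V, so this man scores 5600 ml whatever he loses. In the 300 ml case with one postoperative unit, the printed formula gives 120/0.0214 = 5600 ml uncounted and 300/0.0214 = 14,000 ml counted. Correcting the transfusion window alone does not make the output usable.

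**The case against.** **The formula itself sets no window.** True, but the text introducing it names intraoperative transfusions twice, once as the reason for choosing the method. An untimed term does not override that. At best the section is ambiguous, and the same wording change resolves it.

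**The three sampling times can be reconciled.** Largely so: they read as a nominal time, a minimum and a range, and {18a} refers to a standard operating procedure that equalises sample timing across sites. The different wordings are a point of tidiness. The mismatch does not depend on them, since all three place the draw at 6 h or later.

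**The primary outcome may be untouched.** This stands. The suction and weighing method needs neither hematocrit nor transfusion data, and the article does not say that the hematocrit method supplies the analysed value.

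**Stronger readings that the documents do not support.** A reader might infer that the rule hides loss mainly in the heaviest bleeders and so biases the comparison toward no effect. Heavy bleeders are plausibly transfused more often after surgery, but the documents give no postoperative transfusion rate, overall or by arm, and Step 4 shows opposing errors that may also be larger in the same patients. Nor does the 62% describe a heavy bleeder: 849 ml is about 4.4% BSA excised at the plan's mean of 194 ml/% BSA. The 700 ml case (2205 ml, about 11.4% BSA) gives 29%.

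A reader might also try a power calculation. One uncounted 180 ml unit in 20% of placebo and 10% of tranexamic acid patients, at mean hematocrit 0.33 and 10% BSA excised, removes 180/0.33/10 × 0.10 = 5.5 ml/% BSA from the difference and takes power from 81% to about 71%. Those rates are invented, and the result applies only if the hematocrit method is the one analysed. It is not a finding.

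**Conclusion.** The point holds for the second measure. As described, the red-cell balance uses transfusions up to the end of surgery and a hematocrit from 6 h or later, and every millilitre of red cells given in that gap and left out lowers calculated red-cell loss by one millilitre. That part is algebra on the protocol's own lines.

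For one patient the error can be large: about 29% at 700 ml red-cell loss and about 62% at 300 ml for a single 180 ml unit. These figures rest on the assumed weight, hematocrit and unit volume, and on a mean-hematocrit denominator that the article does not print. Across the trial, neither the frequency nor the net direction between arms can be derived from the documents. It is a specific and cheap correction to a stated rule, secondary to the denominator error in the same formula.

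**What to change.** In Intervention description {11a}, define the transfused volume as all red cells given from the preoperative sample to the postoperative hematocrit draw. State one draw window in the same words there, in the Fig. 1 legend and in Participant timeline {13}. Label the result as blood loss up to the draw, not intraoperative loss, because it includes postoperative oozing. Make the change together with the correction of the formula's denominator, and before unblinding.

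The cost is small: wording in three places, plus transfusion times and the actual draw time for each patient. Nothing in patient care changes. The alternative is to keep intraoperative transfusions only and pair them with an end-of-surgery hematocrit. That would match the intervals and the phrase during surgery, but it needs a measurement the text does not list, and inclusion has been running since December 2021.

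### The printed hematocrit formula for blood loss divides by the hematocrit drop, which cancels, so a non-transfused patient's result is simply estimated blood volume

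*Protocol article*

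**What the plan says.** Intervention description {11a} sets out two ways of registering blood loss. The first is direct: "Firstly, intraoperative blood loss will be estimated by measuring the volume of blood collected in suction canisters", plus weighed materials, with dry weights and saline subtracted. The second is indirect: "we will calculate blood loss based on the preoperative hematocrit, postoperative hematocrit, and the intraoperative transfusions", using a formula credited to a 2006 publication (reference 21) and chosen because it takes transfusions into account.

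The formula is then printed in four lines:

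- Total blood loss is total red cell loss divided by hematocrit before minus hematocrit after: "total}\;\mathrm{red}\;\mathrm{cell}\;\mathrm{loss}\;(\mathrm{ml})\;/\;(\mathrm{hematocrit}\;\mathrm{before}\;\mathrm{surgery}\;-\;\mathrm{hematocrit}\;\mathrm{after}\;\mathrm{surgery".
- Total red cell loss is the accepted loss plus transfused cells: "accepted}\;\mathrm{red}\;\mathrm{cell}\;\mathrm{loss}\;(\mathrm{ml})\;+\;\mathrm{volume}\;\mathrm{of}\;\mathrm{transfused}\;\mathrm{red}\;\mathrm{blood}\;\mathrm{cells".
- Accepted red cell loss is blood volume times the same hematocrit difference: "Estimated}\;\mathrm{volume}\;\ast\;(\mathrm{hematocrit}\;\mathrm{before}\;\mathrm{surgery}\;-\;\mathrm{hematocrit}\;\mathrm{after}\;\mathrm{surgery".
- Estimated blood volume is 70 ml/kg in men and 65 ml/kg in women.

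Plans for assessment and collection of outcomes {18a} presents the use of two measurements as a gain in accuracy. Outcomes {12} gives the primary outcome as ml per % BSA excised, measured during surgery, without naming the method that supplies it.

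**The concern.** The hematocrit difference appears once as a multiplier, in the accepted red cell loss, and once as the divisor of the final step. A quantity that is multiplied in and then divided out leaves no trace, so the calculated blood loss cannot respond to the hematocrit change it is meant to use. To turn a volume of red cells into a volume of blood, one divides by the hematocrit of the blood that was shed, which is a level and not a difference.

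At stake is one of only two blood-loss measures in a trial whose question is blood loss. Computed as printed, it says nothing about bleeding in non-transfused patients. It also misbehaves in transfused patients, the case for which the formula was chosen. It could then neither support nor cross-check the directly measured volume.

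**Working it through.** **Inputs.** Write V for estimated blood volume, H0 and H1 for hematocrit before and after surgery, and T for the volume of transfused red cells. The four definitions are those printed in Intervention description {11a}. The document gives no worked example of the formula, so there is no plan figure to reproduce. The weight, hematocrits and transfused volumes below are my illustrations.

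**Algebra.**

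1. Accepted red cell loss = V × (H0 − H1).
2. Total red cell loss = V × (H0 − H1) + T.
3. Total blood loss = [V × (H0 − H1) + T] / (H0 − H1) = V + T / (H0 − H1).

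Three consequences follow:

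- If T = 0, the result is V for any non-zero change in hematocrit, including a rise. If hematocrit does not change, the result is 0/0 and undefined.
- If T > 0 and hematocrit falls, the result always exceeds V, and it gets smaller as the fall gets larger.
- If T > 0 and hematocrit rises by a small amount, the result is negative.

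**Numbers.** For an 80 kg man, V = 80 × 70 = 5600 ml. The last column divides the same red cell loss by (H0 + H1)/2. That divisor is an assumption, used only to show what a working version would give.

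| H0 → H1 | T (ml) | Red cell loss (ml) | As printed (ml) | Divided by mean hematocrit (ml) |
|---|---|---|---|---|
| 0.36 → 0.31 | 0 | 5600 × 0.05 = 280 | 280 / 0.05 = 5600 | 280 / 0.335 = 836 |
| 0.36 → 0.34 | 0 | 5600 × 0.02 = 112 | 112 / 0.02 = 5600 | 112 / 0.35 = 320 |
| 0.36 → 0.34 | 300 | 112 + 300 = 412 | 412 / 0.02 = 20,600 | 412 / 0.35 = 1177 |
| 0.34 → 0.35 | 300 | −56 + 300 = 244 | 244 / (−0.01) = −24,400 | 244 / 0.345 = 707 |

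The reversed direction shows when T is held at 180 ml and hematocrit starts at 0.40. For falls of 0.01, 0.02, 0.05 and 0.10 the printed formula gives 23,600, 14,600, 9200 and 7400 ml. The largest fall gets the smallest loss.

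**Sensitivity to the replacement divisor.** With no transfusion and hematocrit falling from 0.40 to 0.39, 0.38, 0.35 and 0.30, the mean-hematocrit divisor gives 142, 287, 747 and 1600 ml. The preoperative hematocrit as divisor gives 140, 280, 700 and 1400 ml. Either makes the result follow the loss; the printed version gives 5600 ml in all four cases.

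**Against the plan's own scale.** Eligibility criteria {10} works with 100–200 cc per % BSA excised, and Sample size {14} with a mean of 194 ml per % BSA. For a 2% excision in this man without transfusion, the printed formula gives 5600 / 2 = 2800 ml per % BSA, about 14 times the planning mean (2800 / 194 = 14.4).

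**What is not affected.** The sample size reproduces. A 25% reduction of 194 is 48.5; with SD 81, two-sided 5% and 80% power, the t-test calculation gives 44.8, so 45 per arm. Then 90 / 0.95 = 94.7, so 95 patients. None of this uses the hematocrit formula.

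**The case against.** The algebra cannot be disputed. The case on the other side concerns how much it matters.

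- **It may be a transcription slip.** The text refers to a published formula, and the trial's database or code may hold the right version. That is possible and cannot be checked from the article. But the article prints only this definition, with the subtraction explicit in both lines, so a reader or programmer following it would build the wrong quantity.
- **The primary outcome probably comes from the other method.** Outcomes {12} speaks of loss measured during surgery, and the direct method fits that better than a calculation needing a sample taken 6 h or more after surgery. This is a fair reading and limits the consequence. It is not settled, because no method is named and section {18a} relies on having two.
- **A between-arm comparison of the printed value would not be exactly zero.** This stands. The value varies with weight and sex, and with excised area once expressed per % BSA. Any arm difference among non-transfused patients would reflect those factors and not bleeding.
- **The documents do not establish the mean hematocrit as the divisor.** This also stands. The comparison column above rests on an assumption, and the correction has to be confirmed in the cited source.
- **The error is recoverable.** If weight, both hematocrits and transfused volumes are recorded, the right value can be computed at analysis. That makes the repair cheap but does not make the printed definition usable.

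**Conclusion.** The concern holds. As printed, the formula reduces exactly to estimated blood volume plus transfused red cells divided by the hematocrit drop. In non-transfused patients it carries no information on bleeding: an 80 kg man is assigned 5600 ml at any non-zero change in hematocrit, where a working version gives a few hundred millilitres for modest falls. In transfused patients it gives more than total blood volume when hematocrit falls and can give large negative volumes when hematocrit rises.

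The cancellation needs no assumption. The illustrative sizes depend on the chosen weight, hematocrits and transfused volume, and the comparison values also on the assumed divisor. The defect is confined to the calculated method; it reaches the primary outcome only if that method feeds it, which Outcomes {12} leaves open. The formula must be corrected before it is used.

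**What to change.** Replace the denominator of the total blood loss line with a hematocrit level. The mean of the before and after values, (H0 + H1)/2, is the natural candidate, to be confirmed against the source the protocol cites. Then check whether any database field or analysis code was built on the printed version, and recompute where it was.

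A minor tidy-up belongs with this. The formula needs a preoperative hematocrit, but the pre-surgery panel lists hemoglobin without it, while the postoperative line reads "after surgery: hemoglobin and hematocrit". Hematocrit should be added to the pre-surgery list.

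The cost is one line of text and a code check. Hematocrit comes from the same blood sample as hemoglobin, so no extra sampling is needed. Trial status gives December 2025 as the expected end of inclusion, and the correction should be made before analysis.
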